# Efficacy and safety of 5% lidocaine patches for postoperative pain management in patients undergoing unilateral inguinal hernia repair: study protocol for a prospective, double-blind, randomized, controlled clinical trial

**DOI:** 10.1186/s13063-022-06700-3

**Published:** 2022-09-11

**Keywords:** Topical analgesics, Lidocaine patch, Inguinal hernia repair

## Abstract

**Background:**

Acute postoperative pain is a common complication of inguinal hernia repair. Pain management using local application of anesthetic agents over the skin surrounding the surgical incision may reduce the requirement for other pain medications. Targeted topical analgesics such as 5% lidocaine patches have been known to improve acute and chronic pain. However, the clinical effect of lidocaine patches on postoperative pain after inguinal hernia repair has not been studied, especially in patients undergoing surgery at day surgery units.

**Methods/design:**

This is a single-center, prospective, double-blind, randomized, controlled clinical trial. Participants with unilateral inguinal hernia will be randomized to the lidocaine patch group or the placebo patch group. Based on the randomized allocation sequence, either lidocaine patches or placebo patches will be attached near each participant’s surgical wound after open hernia repair under general anesthesia. Participants will be asked to follow up at our outpatient clinic on the first postoperative day and at 1 week after surgery. The primary outcome is pain intensity, which will be measured using the visual analog scale (VAS) at the time of discharge from the day surgery unit. The secondary outcomes are VAS score at 24 h and 1 week after surgery. We will collect and analyze the participants’ clinical data (amount of intraoperative opioid use, time to recovery, and pain intensity at 30 min after surgery) and demographic characteristics (age, sex, body weight, and height).

**Discussion:**

This trial may not only provide evidence on the efficacy of a 5% lidocaine patch for acute postoperative pain management after unilateral inguinal hernia repair, but also demonstrate the efficacy and safety of the patch for post-discharge pain management.

**Trial registration:**

ClinicalTrials.gov NCT04754451. Registered on February 10, 2021.

**Supplementary Information:**

The online version contains supplementary material available at 10.1186/s13063-022-06700-3.

## Background

Inguinal hernia repair is a commonly performed in general surgery. Acute postoperative pain, which can be moderate to severe in intensity, commonly occurs after open inguinal hernia repair [1, 2]. The intensity of pain after open inguinal hernia repair has been reported to be the highest on the first postoperative day [1]. Untreated postoperative pain or a high pain score within 24 h of surgery may lead to persistent pain after inguinal hernia repair [3, 4]. Patients with prolonged pain have an increased duration of hospitalization and may fail to return to their daily lives [5]. For these reasons, various modalities, such as pain medication and nerve block, have been used for postoperative pain management [3, 6].

Acute postoperative pain is primarily managed with intravenous or oral administration of narcotic or non-narcotic analgesics. However, most of these drugs are systemically administered, which may result in complications such as nausea, vomiting, inhibition of bowel motility, and abdominal discomfort. These adverse effects can occur even after discharge from the hospital, especially in patients undergoing day surgery for inguinal hernia repair.

On the other hand, pain management with topical applied analgesics near the surgical incision site may reduce the incidence of complications and drug interactions [7]. A lidocaine patch is a pain management modality that involves local infiltration of an analgesic. The use of a 5% lidocaine patch has only been approved by the Food and Drug Administration for treating neurologic pain due to herpes zoster infection; it has not been approved for acute postoperative pain management [8].

Several studies have demonstrated the positive effects of lidocaine patches on acute postoperative pain [9, 10]. However, to the best of our knowledge, there are no studies on the clinical effects of lidocaine patches for acute postoperative pain management after inguinal hernia repair, especially in patients admitted to day surgery units. Furthermore, the use of a lidocaine patch may minimize the systemic effects of the analgesic agent and reduce the financial burden on the patient by decreasing the requirement for the extra pain medication. Therefore, we designed this double-blind, randomized, controlled clinical trial to determine the efficacy and safety of a 5% lidocaine patch for postoperative pain management in patients undergoing unilateral inguinal hernia repair at a day surgery unit.

## Methods/design

### Study design

This is a single-center, prospective, superiority, double-blind, randomized, controlled clinical trial. This study has been approved by the Institutional Review Board (B-2007-625-006) of Seoul National University Bundang Hospital. Written informed consent to participate will be obtained by the principal investigator at the time of screening for eligibility on the patient’s initial visit to outpatient clinic. After surgery, the experimental group will receive 5% lidocaine patches (Lidotop Cataplasma; SK chemical Co. Ltd, Seongnam, Korea), and the control group will receive placebo patches that were specially made for this study. The comparator is a well-made placebo patch to evaluate not only the efficacy but also the safety of the 5% lidocaine patch. The overview of the study design is shown in Fig. 1.

**Fig. 1 Fig1:**
[figure not shown]
Trial design flowchart. VAS, visual analog scale; POD, postoperative day

### Hypothesis

Evaluating the efficacy of a 5% lidocaine patch on acute postoperative pain in a patient undergoing unilateral inguinal hernia repair at a day surgery unit is the main purpose of this study. This prospective, superiority, double-blind, randomized, controlled clinical trial was designed based on the hypothesis that patients who applied the lidocaine patch will have a lower VAS score at discharge after surgery than patients who applied the placebo patch after unilateral inguinal hernia repair at a day surgery unit.

### Inclusion and exclusion criteria

The inclusion criteria are (a) age between 19 and 80 years, (b) American Society of Anesthesiologists risk classification score of I (healthy) or II (mild systemic disease), (c) elective open surgery for unilateral inguinal hernia, and (d) admission to and discharge from the day surgery unit on the day of the surgery itself.

The exclusion criteria are (a) obesity (body mass index > 30 kg/m^2^), (b) renal insufficiency (serum creatinine level ≥ 1.4 mg/dL), (c) liver insufficiency (serum aspartate transferase level ≥ 120 IU/L or serum alanine transaminase level ≥ 120 IU/L), (d) known hypersensitivity to amide-based local anesthetics, (e) use of class I antiarrhythmic medication such as tocainide and mexiletine, and (f) refusal to participate.

The principal investigator of this study will not exclude patients who are likely to participate in this study based on race or socioeconomic status. Every effort will be made to ensure that as many patients as possible who meet the inclusion criteria will be included. Patients will be informed of the purpose of the study so that they can represent the entire population of patients undergoing general anesthesia.

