### Sample size calculation

The sample size for the primary outcome (VAS score at the time of discharge) was determined based on a previous study on patients with ventral hernia that compared the VAS scores of a control group (4.8 ± 1.4) with those of a lidocaine patch group (3.1 ± 1.6) and observed a difference of 1.7 [9]. For a one-sided analysis with a type I error (α) of 5% and a power (1-β) of 0.8, the number of participants required per group is 14. Anticipating a dropout rate of 10%, the number of participants required per group is 16, resulting in a total sample size of 32.

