### Randomization

We will randomize the participants in a 1:1 ratio to the lidocaine patch group or the placebo patch group. We will achieve block randomization using Random Allocation Software (Isfahan University of Medical Sciences, Isfahan, Iran). A research nurse from the anesthesiology department who is not involved in the study will generate the randomized allocation sequence and deliver the allocated patches. The patches will be given directly to the anesthesiologist and surgeon responsible for applying it at the end of the surgery. The participants and researchers (the anesthesiologist and surgeon) who evaluate the patients’ clinical parameters will be blinded to the group allocation.

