**Fig. 2 Fig2:**
[figure not shown]
Location of the patch. Irrespective of the type of patch used (5% lidocaine or placebo), one patch will be applied 1 cm above and another 1 cm below the surgical wound

Before discharge from the day surgery unit, we will allow participants to use additional pain medications such as opioids or non-steroidal anti-inflammatory drugs as needed during their recovery from the general anesthesia. Either fentanyl (50 μg; Hana fentanyl citrate, Hana Pharm. Co., Ltd, Seoul, Korea) or ketorolac (30 mg; Trolac, Whan In Pharm. Co., Ltd, Seoul, Korea) will be prescribed. Fentanyl will be prescribed a maximum of three times when a patient experiences pain with a VAS score of > 5. Ketorolac will be prescribed if a patient experiences any adverse effects following fentanyl administration. Oral medications such as tramadol/acetaminophen (37mg/325 mg; Rapicet, Chong Kun Dang Pharm. Co., Seoul, Korea) will be prescribed to each patient at the time of discharge for pain management. However, additional pain medication or interventions outside of the protocol during the study period, which is from the surgery to 1 week after surgery, are prohibited.

This study protocol includes criteria for discontinuing intervention. If a participant withdraws their consent, decides to undergo extra surgery besides the unilateral inguinal hernia repair after random allocation, or if any adverse effects with local anesthetics are shown, they will discontinue the study.

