### Outcomes

The primary outcome is pain intensity measured using the VAS at the time of discharge from the day surgery unit, which is approximately 2 or 3 h after the surgery. We will evaluate each patient’s VAS scores in three situations: at rest, when coughing, and when moving. The secondary outcomes are pain intensity at 24 h and 1 week after surgery. We will evaluate each patient’s VAS score when they visit the clinic for wound dressing on the first postoperative day when the pain-relieving effect of the patch has been worn off. At the follow-up visit 1 week after surgery, we will assess the VAS score, the rates of postoperative complications (such as nausea, vomiting, and desaturation), and the total amount of oral combination analgesics used after discharge. To understand the correlation with general anesthesia and lidocaine patch, we will additionally analyze the amount of intraoperative opioid use, time to recovery, and pain intensity at 30 min after surgery as a part of the secondary outcomes. The participants’ demographic characteristics, such as age, sex, body weight, and height, will also be recorded.

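### Eligibility is worded as actual same-day discharge and the primary VAS is read at that same event, so both are settled only after the patch is on and may depend on pain

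*Protocol article*

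**What the plan says.** All references are to the protocol article.

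- **Inclusion and exclusion criteria**, item (d), requires "admission to and discharge from the day surgery unit on the day of the surgery itself". The wording describes something that has happened. It does not say planned or scheduled.
- **Study design** places consent "at the time of screening for eligibility on the patient’s initial visit to outpatient clinic", which is before surgery.
- **Randomization**: "The patches will be given directly to the anesthesiologist and surgeon responsible for applying it at the end of the surgery". Allocation and treatment therefore both come before discharge.
- **Outcomes** sets the primary VAS "at the time of discharge from the day surgery unit, which is approximately 2 or 3 h after the surgery". The other VAS readings in that section have nominal clock times: 30 min, 24 h and 1 week.
- **Procedure** (text after Fig. 2), on rescue before discharge: "Fentanyl will be prescribed a maximum of three times when a patient experiences pain with a VAS score of > 5". The grounds for discontinuation listed there are withdrawal of consent, extra surgery, and a third, "if any adverse effects with local anesthetics are shown, they will discontinue the study". An overnight stay is not among them.
- **Background**: "Patients with prolonged pain have an increased duration of hospitalization".

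**The concern.** An eligibility criterion should be decidable before randomisation. Criterion (d), as worded, cannot be. It depends on how the patient fares after the patch is on, and pain is one plausible reason for not going home. If it is applied as written, patients are selected after allocation on something related to the outcome.

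The primary reading hangs on the same event. A patient who needs repeated rescue may leave later and be scored later, after more treatment, while a comfortable patient is scored early. If the patch works as hypothesised, both effects fall more on the placebo arm. High placebo scores would then be lost or softened, and the estimated difference would shrink. With 16 patients per arm, a single lost patient is 1/16 = 6% of an arm.

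**Working it through.** **1. Order of events.** Screening at the outpatient visit, then surgery, then patch at the end of surgery, then recovery with rescue if VAS exceeds 5, then discharge with the primary VAS. Criterion (d) and the primary time point are both fixed by the last step. At screening, only the plan to discharge on the same day can be known.

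**2. The patient kept overnight.** Under criterion (d) this patient fails inclusion after allocation. Under the discontinuation list the patient stays in. There is no same-day discharge reading in either case. The article does not reconcile the two.

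**3. The plan's own figures.** The Sample size calculation section cites a "control group (4.8 ± 1.4) with those of a lidocaine patch group (3.1 ± 1.6) and observed a difference of 1.7".
- Difference: 4.8 − 3.1 = 1.7.
- Pooled SD: √((1.4² + 1.6²)/2) = 1.503. Standardised effect: 1.7/1.503 = 1.13.
- At 80% power and 5% alpha, a two-sided t-test needs 13.3, rounded up to 14 per group, which matches the plan. The one-sided test that the plan names needs 10.4, rounded up to 11. That mismatch is a separate matter, so power is shown both ways below.
- Dropout: 14/0.90 = 15.6, rounded up to 16 per group and 32 in total, as stated.

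**4. Illustration of selective loss.** Assumptions: VAS is normal with the means and SDs above, and every patient above a cut-off c is not discharged that day and is lost. The cut-offs are assumed; none comes from the article. With a = (c − μ)/σ:
- proportion lost = 1 − Φ(a)
- mean of those kept = μ − σ·φ(a)/Φ(a)

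Cut-off 7:
- Placebo: a = (7 − 4.8)/1.4 = 1.571; lost 5.8%; mean 4.8 − 1.4 × 0.1161/0.9420 = 4.628.
- Lidocaine: a = (7 − 3.1)/1.6 = 2.438; lost 0.7%; mean 3.1 − 1.6 × 0.0205/0.9926 = 3.067.
- Difference: 1.56.

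Cut-off 6:
- Placebo: a = 0.857; lost 19.6%; mean 4.8 − 1.4 × 0.2763/0.8043 = 4.319.
- Lidocaine: a = 1.813; lost 3.5%; mean 3.1 − 1.6 × 0.0772/0.9650 = 2.972.
- Difference: 1.35.

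Power is for a t-test with 16 randomised per arm at 5% (exact with no loss, simulated otherwise):

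| Assumed cut-off | Lost, placebo / lidocaine | Difference | SD of those kept | Standardised effect | Power, one-sided / two-sided |
|---|---|---|---|---|---|
| none | 0 / 0 | 1.70 | 1.50 | 1.13 | 93% / 87% |
| 7 | 5.8% / 0.7% | 1.56 | 1.41 | 1.11 | 91% / 84% |
| 6 | 19.6% / 3.5% | 1.35 | 1.29 | 1.04 | 85% / 75% |
| 5 | 44% / 12% | 1.06 | 1.12 | 0.95 | 67% / 52% |

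If only half of those above 6 were lost (10% placebo, 2% lidocaine), the difference would be 1.55. At cut-off 6 with full loss, placebo loss is about twice the 10% dropout allowance.

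**5. Timing.** No calculation is possible. The article gives neither discharge criteria nor the course of VAS between 2 and 3 h.

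**The case against.** The strongest reply is that (d) simply means patients booked as day cases. Eligibility is screened before surgery, and criterion (c), elective open repair, is also a future event at that point. The Discussion speaks of enrolling patients who have their repair at a day surgery unit. On that reading the exclusion problem is one missing word. This is a fair reading and may well be the intended one, but the text does not say it, and the event-driven primary time point remains either way.

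A reader might infer that the patients in most pain do drop out or are scored later, and that the randomised comparison is broken. The documents do not support that. Overnight stay is not a listed ground for discontinuation. No discharge criteria are given, so a link between pain and discharge time is inferred. The Background sentence on hospital stay concerns prolonged pain, not an hour's delay in a day unit. The indicated 2 to 3 h also limits the drift, though it is not binding.

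The illustration has limits too. Its cut-offs are assumed, it ignores rescue given above VAS 5, and its means come from laparoscopic ventral hernia repair. Truncation also reduces the SD, so the standardised effect moves less than the raw difference. At cut-offs 7 and 6, one-sided power stays above the planned 80%.

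Nor could this mechanism be expected to create a false claim for the patch. Without a patch effect, selection through pain alone should act alike in both arms.

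Finally, VAS at discharge is the stated hypothesis and a legitimate endpoint for day surgery, so moving the primary reading is more debatable than rewording (d). Analysis sets are usually left to an analysis plan. Eligibility wording and the primary time point are protocol content, and no later plan can recover a reading that was not taken at a common time.

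**Conclusion.** The point holds as a risk created by the wording. Criterion (d) is a post-treatment event as written, and the primary VAS is tied to that event with only an approximate time. Two things are established from the text: an overnight patient's status is contradictory, and the primary reading time is not common to all patients. That pain drives either one is a plausible inference, not a documented fact.

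The number of patients affected is unknown. Under full loss above an assumed cut-off of 7 or 6, the difference falls from 1.70 to about 1.56 or 1.35, with modest loss of power. Only the more extreme cut-off of 5 costs much power. The expected direction, if the patch works, is toward no difference. The change is worth making because it costs little and protects a trial of 32 patients from selection and timing that depend on the outcome.

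**What to change.** 1. Reword (d) as *scheduled for day surgery with planned same-day discharge*, judged before randomisation.
2. State that all randomised patients are analysed in their allocated arm, including those kept overnight.
3. Take the primary VAS within one fixed, narrow window after patch application, inside the stated 2 to 3 h period, whether or not the patient has been discharged.
4. Keep VAS at actual discharge and time to discharge as secondary outcomes, so the question in the Hypothesis section is still answered.

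**Cost.** The sample size does not change: 14 per group, 16 with dropout. The primary reading is no longer exactly at discharge, and staff must take it at a set time. A common reading time does not remove the influence of rescue given beforehand.

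**If enrolment is over.** Trial status gives a start in March 2021 and predicted completion in October 2021, so the design changes may come too late. The sponsor can then still analyse all randomised patients in their allocated arms and report overnight stays and discharge times by arm, so that readers can judge whether either differed.

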### Sample size calculation

The sample size for the primary outcome (VAS score at the time of discharge) was determined based on a previous study on patients with ventral hernia that compared the VAS scores of a control group (4.8 ± 1.4) with those of a lidocaine patch group (3.1 ± 1.6) and observed a difference of 1.7 [9]. For a one-sided analysis with a type I error (α) of 5% and a power (1-β) of 0.8, the number of participants required per group is 14. Anticipating a dropout rate of 10%, the number of participants required per group is 16, resulting in a total sample size of 32.

### Randomization

We will randomize the participants in a 1:1 ratio to the lidocaine patch group or the placebo patch group. We will achieve block randomization using Random Allocation Software (Isfahan University of Medical Sciences, Isfahan, Iran). A research nurse from the anesthesiology department who is not involved in the study will generate the randomized allocation sequence and deliver the allocated patches. The patches will be given directly to the anesthesiologist and surgeon responsible for applying it at the end of the surgery. The participants and researchers (the anesthesiologist and surgeon) who evaluate the patients’ clinical parameters will be blinded to the group allocation.

### Procedure

All participants will undergo unilateral inguinal hernia repair under general anesthesia. As pre-treatment, each patient will be injected with 0.03 mg/kg of midazolam on arrival at the operating room. An anesthesiologist will induce and maintain general anesthesia with inhaled anesthetics and opiates using conventional methods. A general surgeon will make a transverse incision of approximately 3 to 4 cm along the skin fold line and perform routine Lichtenstein tension-free mesh inguinal hernia repair. The skin will be closed with subcutaneous interrupted sutures, and skin bond (7 mm × 60 mm; Leukosan SkinLink, BSN medical, Hamburg, Germany) will be applied. After covering the surgical wound with aseptic dressing, lidocaine or placebo patches will be applied near the surgical wound based on the randomized allocation sequence. Each patient will receive two patches, which will be placed 1 cm above and 1 cm below the surgical wound (Fig. 2).

**Fig. 2 Fig2:**
[figure not shown]
Location of the patch. Irrespective of the type of patch used (5% lidocaine or placebo), one patch will be applied 1 cm above and another 1 cm below the surgical wound

Before discharge from the day surgery unit, we will allow participants to use additional pain medications such as opioids or non-steroidal anti-inflammatory drugs as needed during their recovery from the general anesthesia. Either fentanyl (50 μg; Hana fentanyl citrate, Hana Pharm. Co., Ltd, Seoul, Korea) or ketorolac (30 mg; Trolac, Whan In Pharm. Co., Ltd, Seoul, Korea) will be prescribed. Fentanyl will be prescribed a maximum of three times when a patient experiences pain with a VAS score of > 5. Ketorolac will be prescribed if a patient experiences any adverse effects following fentanyl administration. Oral medications such as tramadol/acetaminophen (37mg/325 mg; Rapicet, Chong Kun Dang Pharm. Co., Seoul, Korea) will be prescribed to each patient at the time of discharge for pain management. However, additional pain medication or interventions outside of the protocol during the study period, which is from the surgery to 1 week after surgery, are prohibited.

This study protocol includes criteria for discontinuing intervention. If a participant withdraws their consent, decides to undergo extra surgery besides the unilateral inguinal hernia repair after random allocation, or if any adverse effects with local anesthetics are shown, they will discontinue the study.

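### The discontinuation rule removes randomised participants who have extra surgery from the trial, not only from the patch, so their later outcomes may never be collected

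*Protocol article*

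**What the plan says.** All references are to the protocol article.

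- **Procedure, last paragraph (after Fig. 2).** The paragraph opens with "This study protocol includes criteria for discontinuing intervention". It lists three triggers: withdrawal of consent, a participant who "decides to undergo extra surgery besides the unilateral inguinal hernia repair after random allocation", and adverse effects of local anaesthetic. It closes with "if any adverse effects with local anesthetics are shown, they will discontinue the study". The stated consequence, which applies to all three triggers, is therefore leaving the study.
- **Inclusion and exclusion criteria.** Criterion (c) is "elective open surgery for unilateral inguinal hernia".
- **Randomization.** "We will randomize the participants in a 1:1 ratio". On delivery: "The patches will be given directly to the anesthesiologist and surgeon responsible for applying it at the end of the surgery". The moment at which a participant is allocated is not given.
- **Outcomes.** The primary VAS is taken "at the time of discharge from the day surgery unit, which is approximately 2 or 3 h after the surgery". A secondary VAS is taken at 24 h. The 1-week visit collects the VAS, oral analgesic use after discharge and "the rates of postoperative complications (such as nausea, vomiting, and desaturation").
- **Sample size calculation.** 14 per group, raised to 16 per group (32 in total) for 10% dropout.

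**The concern.** Stopping a study treatment and ending a participant's follow-up are different acts. This paragraph announces the first and prescribes the second. A randomised participant then leaves because of something that happened after randomisation, and the comparison for any later outcome no longer rests on the groups as allocated.

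The definition of analysis sets can reasonably be left to an analysis plan that is not shown. This point is different, because no analysis plan can recover a 24 h or 1-week assessment that was never made.

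What is at stake depends on which surgery the clause means, and the text does not settle that:

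- **Procedure added at or before the index operation.** The participant leaves before discharge, so the primary VAS may be lost. An allocation is used up without yielding the outcome.
- **Surgery later in the study week.** The primary VAS will normally have been recorded. The 1-week VAS, analgesic use and complication assessment may be lost, and possibly the 24 h VAS.

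The trial's title and stated purpose include safety, and the arms are small, so a single missing complication matters.

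**Working it through.** **1. Set the passages side by side.** The opening of the Procedure paragraph concerns the intervention; its closing words concern the study. Outcomes places assessments at discharge, 24 h and 1 week. A participant who has left the study would not be expected to attend the visits that follow.

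**2. Reproduce the plan's dropout arithmetic.** 14 / (1 − 0.10) = 15.6, rounded up to 16 per group, 32 in total. This matches the article. The allowance is 16 − 14 = 2 participants per group.

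**3. How many might be affected?** The article gives no rate of extra surgery. Assume a rate q of 1% to 5%.
- Expected number = 32q: 32 × 0.01 = 0.3 and 32 × 0.05 = 1.6.
- Chance of at least one = 1 − (1 − q)^32: 27.5% at q = 1%, 62% at 3%, 81% at 5%.
- Chance that at least one arm of 16 loses more than its allowance of 2 = 1 − [P(X ≤ 2)]², with X binomial(16, q): about 0.1% at q = 1%, 2% at 3%, 8% at 5%. At 5%, for example, P(X ≤ 2) = 0.440 + 0.371 + 0.146 = 0.957, and 1 − 0.957² = 0.08.

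**4. Cost in power for the primary outcome.** Inputs from Sample size calculation: difference 1.7, SDs 1.4 and 1.6. The pooled SD is √[(1.4² + 1.6²)/2] = 1.503. Power comes from the noncentral t distribution with 2n − 2 degrees of freedom and noncentrality 1.7 / (1.503 × √(2/n)).

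| n per arm | One-sided 5% (as stated) | Two-sided 5% |
|---|---|---|
| 16 | 0.93 | 0.87 |
| 14 | 0.90 | 0.82 |
| 13 | 0.88 | 0.79 |
| 12 | 0.85 | 0.75 |
| 11 | 0.82 | 0.71 |

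On the stated one-sided test, power stays above the planned 0.80 down to 11 per arm. Both columns are shown because 14 per group is what a two-sided 5% t-test needs, whereas a one-sided one needs 11. The present point does not depend on that mismatch. Surgery after discharge from the unit would cost no primary-outcome power at all.

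**5. Cost to a complication rate.** Suppose one participant in an arm of 16 has a complication.
- Kept in follow-up: 1/16 = 6.3%, exact 95% interval 0.2% to 30.2%.
- Removed, together with the event: 0/15 = 0%, upper limit 1 − 0.025^(1/15) = 21.8%.

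One removal is enough to change the report from an observed event to none.

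**The case against.** The strongest case against is that this is loose wording from which too much can be read. Several parts of that case stand.

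- **Reoperation.** A reader might infer that reoperated patients disappear from the 1-week complication count. The documents do not support that. They never mention reoperation, and their examples of complications are nausea, vomiting and desaturation. A participant who decides on surgery besides the hernia repair could equally be having an unrelated or added elective procedure.
- **Data already collected.** Nothing says that earlier data, or the event that triggered discontinuation, are discarded. Data monitoring also describes separate reporting of adverse drug reactions. How discontinued participants are analysed may be set out in a document not shown.
- **Time of allocation.** A reader might infer that patients are allocated before surgery and then excluded on eligibility. The article does not say when allocation occurs, and its wording is also compatible with allocation at closure.
- **Bias between arms.** If the decision precedes patch application and is made under blinding, it should be little related to arm.
- **Power.** A reader might set the 62% to 81% chance of a loss (at an assumed 3% to 5%) beside the fall in power at 13 or 12 per arm. These are different events. The first is any loss among 32; the second needs losses beyond the dropout allowance, which is far less likely.
- **The adverse-effect trigger.** The same sentence ends participation for adverse effects of local anaesthetic, which threatens safety counts more directly. That is true, and a repair confined to the extra-surgery clause would leave it in place.

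What the objection does not remove is the rule itself. The text gives leaving the study as the consequence, and ambiguity about which surgery triggers it is a further reason to clarify.

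**Conclusion.** The point holds in a limited form. The Procedure paragraph contradicts itself on whether its criteria end the intervention or end participation. As written, extra surgery after allocation is a post-randomisation exclusion that may stop collection of whichever outcomes are still to come.

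The size is modest. At an assumed 1% to 5%, 0.3 to 1.6 of 32 participants would be affected, and the existing dropout allowance would usually absorb them. The effect on power for the primary outcome is minor. The material risk is to the 1-week outcomes and the safety description, and possibly the 24 h VAS, where one lost event in an arm of 16 moves 6.3% to 0%.

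This rests on two assumptions: the unsourced 1% to 5% range, and that leaving the study means no further assessments. It does not rest on any claim about reoperation, about when allocation takes place, or about data being deleted.

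**What to change.** 1. Reconcile the opening and closing phrases of the Procedure paragraph. State separately what ends the intervention and what ends participation. The clinical criteria for stopping the patch are for the investigators to settle.
2. State which surgery the clause covers: a procedure added at the index operation, a later one within the study week, or both.
3. State that every randomised participant is followed to 1 week for all outcomes, in the assigned arm, whatever the reason for discontinuing the intervention, unless consent is withdrawn. Record any further surgery, with its date and reason. Wording the rule this way also covers the adverse-effect trigger in the same sentence.
4. Since the patch is applied only after closure and dressing, state that allocation is assigned at wound closure, once the surgeon has confirmed that the qualifying operation was performed, if this is not already the practice. Patients with an added procedure would then not be randomised.

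The cost is protocol wording, a few more follow-up contacts and minor theatre logistics. The research nurse already delivers the patches for use at the end of surgery, and the sample size does not change.
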